##### Criteria for early termination

2.8.7.2

1.Patients whose symptoms have improved during the study, who request to terminate early, and who no longer require treatment at the discretion of the investigators can terminate the study earlier than planned.2.Patients who have terminated the study early are not classified as withdrawn/discontinued patients and are considered to have complied with the study treatment.

#### Data collection, access, and management

2.8.8

All information regarding the patient is anonymized through initial processing, and all investigators are obliged to maintain confidentiality of the results. The source document is registered immediately when the data are collected, and it will be recorded in the CRF. All the documents of the trial will be kept safe, and only those who have been approved by the principal investigator will have access to all data related to the trial.

Data management of this clinical trial will be conducted in accordance with the standard working guidelines of the Catholic Kwandong University Clinical Research Center, and other matters not specified in the protocol will be conducted following the International Council for Harmonization of Technical Requirements for Pharmaceuticals for Human Use guideline for GCP and Korea-GCP standards.

### Statistical analysis

2.9

For efficacy analysis, the intent-to-treat (ITT) group will be mainly analyzed, and secondary analysis will be done on the per-protocol (PP) group. Safety analysis will be performed on the ITT group patients who undergo at least one procedure after randomization. The ITT group will include all patients who have been randomly assigned, undergo at least one follow-up, and are eligible for efficacy assessment. PP group will include patients who satisfy the following conditions:

1.patients who satisfy both selection and exclusion criteria;2.those who have completed the pre-determined minimum number of acupotomy (6 out of 8 sessions); and3.those whose symptoms were improved and who satisfied treatment completion criteria

1.

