# Exploratory evaluation is not conduced for patients who have completed treatment early. For patients who dropped out of the study, exploratory evaluation is conducted after 4 weeks from dropping out (exploratory effectiveness evaluation for dropout participants can be conducted through telephone counseling instead of in-person visits).

∗∗ Evaluation of direct non-healthcare, direct non-healthcare, and lost productivity costs.

†† Those patients who reported adverse reactions will complete EQ-5D by recalling time of adverse events.

Patients who undergo 1 NBT and show continued symptoms (patient's subjective pain improvement is less than 50% after the procedure or the numeric rating scale (NRS) score being 5 or higher) will undergo screening at 1 week after the first procedure. For screening, demographic information, medical history, physical examination, vital signs, questionnaire survey, laboratory test, and selection/exclusion criteria will be evaluated. Randomization and group allocation will be performed at screening and baseline. Fifty patients will be enrolled and randomly divided into 2 groups. Patients who are judged suitable for the study after the screening test and voluntarily agree to participate will be randomly assigned to either the NBT single treatment group (usual care group) or NBT + deeply inserted acupotomy treatment group in a 1:1 ratio (Fig. 1). Thereafter, the randomly assigned patients will undergo primary and secondary outcome evaluations and economic evaluation.

The NBT + deeply inserted acupotomy group will receive 8 acupotomy treatments (at visits 2, 3, 5, 6, 7, 8, 10, and 11) for 4 weeks as well as additional 2 NBTs (at visits 4 and 9) for 4 weeks. Then, the group will be followed-up for 4 weeks after the intervention treatment. The standard care group will undergo two NBTs (at visits 2 and 4) for 4 weeks and will be followed-up for 4 weeks after the intervention treatment. Primary and secondary outcomes, economic evaluation, and assessment of drug administration history will be conducted at visits 1, 6, and 11, and at the end of follow-up. To evaluate safety, evaluation of adverse events, vital signs, and economic feasibility will be conducted at every visit from visit 2 to visit 12. Laboratory tests will be conducted only at screening.

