**Efficacy evaluation**
In the efficacy evaluation, ITT will be treated as the main analysis group, and PP sets will be treated as the secondary analysis group. All statistical analysis will be conducted as two-sided tests with a significance level of 5%. Two-sided 95% confidence interval will be presented. Descriptive statistics will be presented for each treatment group and visit. Descriptive statistics and 95% confidence intervals will be presented for differences between the baseline and each visit.

Among efficacy evaluation variables, missing values of continuous variables will be analyzed using baseline observation carried forward correction.

A. Analysis of primary endpoints

For symptoms of lumbosacral radiculopathy at each measurement time point, descriptive statistics (number of patients, mean, and standard deviation) of the ODI score and changes in ODI at the end of treatment (4 weeks) and follow-up (8 weeks) compared with the baseline will be presented.

Paired *t*-test or Wilcoxon's signed ranked test will be conducted for intra-group changes in ODI at the end of treatment (week 4) compared with the baseline (0) depending on the satisfaction of normality. An analysis of variance model that includes changes in ODI at the end of treatment compared with the baseline as effects and baseline ODI as covariates will be used to evaluate the effects in the treatment group compared with the control group. Differences in least-square mean between treatment and control groups will be calculated, and two-sided 95% confidence interval and *P* value for the differences will be presented.

B. Analysis of secondary endpoint

Changes in ODI at follow-up (8 weeks) compared with baselineAssessment of subjective pain intensity in patients with lumbosacral radiculopathy-Lumbosacral radiculopathy pain will be divided into lower back and lower extremity pain using NRS, MPQ, and K-RMDQAssessment of quality of life related to lumbosacral radiculopathy-Evaluation of overall quality of life using EQ-5D. The same analysis methods for primary endpoints will be used to analyze secondary endpoints

C. Exploratory efficacy evaluation

Evaluation related to additional NBT or surgery after completion of the study

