**4. Economic feasibility evaluation**

Economic feasibility will be evaluated on patients who participated in the clinical trial at least once since visit 2. The economic endpoint to assess cost-effectiveness will be incremental cost-utility ratio, which will be calculated based on the difference in cost and quality-adjusted life year between the experimental and control groups. Quality-adjusted life year will be calculated using EQ-5D measured at the time of visit.

$$\text{ICUR}=\frac{\text{Total Cost}\;(\text{treatment group})-\text{Total Cost}\;(\text{control group})}{\text{Quality-adjusted life year}\;(\text{treatment group})-\text{Quality-adjusted life year}\;(\text{control group})}$$

A. Time horizon

Basic time horizon for analysis will be 4 or 8 weeks. If long-term follow-up beyond 8 weeks is required, the Markov model will be used. Transition probabilities will be estimated based on clinical data collected over 8 weeks. In addition, if the time horizon exceeds 12 months, the unit of cost will be in Korean currency unit (won) for specific years, and a discount rate of 4.5% will be applied based on the economic feasibility evaluation guidelines of the Health Insurance Review and Assessment Service.

B. Analysis perspective

Societal perspective and restricted societal perspectives will be applied to include direct nonhealthcare, direct nonhealthcare, and lost productivity costs.

C. Sensitivity analysis

Deterministic sensitivity analysis will be conducted on all possible parameters and a tornado diagram will be presented. Probabilistic sensitivity analysis will be conducted using the distribution and representative values of all possible parameters. In addition, bootstrap using individual patient level data will be conducted to present the distribution of the economic feasibility evaluation effect index and 95% confidence intervals.

D. Assumptions for missing values

Last-Observation-Carried-Forward analysis method, a conservative method of underestimating missing values in cases where the result is expected to improve over time within the time horizon, is widely used to correct for missing values in clinical studies. Herein, the Last-Observation-Carried-Forward method will be used to assume missing values. In other words, if the patient is withdrawn from the study or completes treatment early, the last measured values will be used for all remaining visits to conduct analysis.

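### The safety set sits inside an 'ITT' set that requires follow-up and efficacy eligibility, so a treated patient who leaves without a qualifying assessment is lost to both the efficacy and the safety analysis

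*Protocol article*

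**What the plan says.** Section 2.9 (Statistical analysis) defines the main set: "The ITT group will include all patients who have been randomly assigned, undergo at least one follow-up, and are eligible for efficacy assessment". The safety population is then taken from that set: "Safety analysis will be performed on the ITT group patients who undergo at least one procedure after randomization". The safety assessment paragraph later in section 2.9 lists the analyses and names no other population.

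For efficacy, "ITT will be treated as the main analysis group, and PP sets will be treated as the secondary analysis group", and "missing values of continuous variables will be analyzed using baseline observation carried forward correction".

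The economic analysis has a third rule: "Economic feasibility will be evaluated on patients who participated in the clinical trial at least once since visit 2".

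The schedule in section 2.2 and Table 1 places outcome evaluation in the combination-arm numbering: it is "conducted at visits 1, 6, and 11, and at the end of follow-up". Adverse events are monitored at every visit after baseline. Table 1 also has an early-termination/drop-out column, which ticks the primary and secondary endpoint evaluations and adverse reaction monitoring.

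**The concern.** An intention-to-treat set should be fixed at randomisation. Here, membership depends on what happens afterwards: attending a follow-up and being judged eligible for efficacy assessment. Neither term is defined. Section 2.6 says that participants and treating investigators cannot be blinded, so the decision to leave can depend on allocation.

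The safety consequence matters more. Whether a patient contributes safety data should depend on exposure, not on having efficacy data. Section 2.8.7.1 foresees drop-out for serious adverse reactions. Because the safety set is nested in ITT, an adverse event already recorded could fall outside the safety analysis when no qualifying follow-up exists. Safety is part of the stated objective (section 1.1), and the added treatment is invasive.

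**Working it through.** **1. Sample size (section 2.3).** 20 per group, inflated for 20% drop-out: 20 / (1 − 0.20) = 25 per group, 50 in total. This reproduces the stated target. One patient is 1/25 = 4 percentage points of an arm.

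**2. Set logic (section 2.9).**
- ITT = randomised AND at least one follow-up AND eligible for efficacy assessment.
- Safety = ITT AND at least one procedure.
- So Safety = randomised AND at least one procedure AND at least one follow-up AND eligible for efficacy assessment.

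The last two conditions exclude treated patients. Nothing elsewhere in section 2.9 readmits them.

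**3. Exposure before the first scheduled outcome visit.** Table 1 puts that visit on Day 12-14 in both arms (combination visit 6, control visit 3).
- Combination arm, acupotomy: the plan gives "8 acupotomy treatments (at visits 2, 3, 5, 6, 7, 8, 10, and 11) for 4 weeks". Visits 2, 3 and 5 come before visit 6, which makes 3 sessions.
- Combination arm, NBT: "additional 2 NBTs (at visits 4 and 9) for 4 weeks". Visit 4 comes before visit 6, which makes 1 block. The total is 3 + 1 = 4 procedures.
- Control arm: NBT at its visits 2 and 4. Only visit 2 (Day 7-8) comes before Day 12-14, so the total is 1 procedure.

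**4. Dependence on the undefined term.**
- If follow-up means an outcome visit, up to 4 procedures (combination) or 1 (control) can precede it, unless the patient attends the drop-out visit.
- If any later visit counts and eligibility adds nothing, fewer patients are lost. One who leaves after the first procedure and never returns is still excluded.
- If the treatment visit itself counts and eligibility adds nothing, nobody treated is lost. The at-least-one-procedure clause would then be largely redundant, because the first post-randomisation visit in each arm is a procedure visit.

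**5. Effect on a reported proportion (illustration).** Suppose one combination patient has a serious event: 1/25 = 4.0%. If that patient leaves unassessed, the written rule gives 0/24 = 0%. Suppose instead that 3 of 25 (12.0%) have an event. Losing one, two or three of them gives 2/24 = 8.3%, 1/23 = 4.3% or 0/22 = 0%.

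**6. Likelihood (assumed rates only).** The documents give no probability q that a treated patient leaves without a qualifying assessment. The expected loss in an arm of 25 is 25q, and the chance of at least one loss is 1 − (1 − q)^25.
- q = 2%: 0.5 patients expected; chance 40%.
- q = 5%: 1.25 patients expected; chance 72%.
- q = 10%: 2.5 patients expected; chance 93%.

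**7. Is the ITT restriction needed?** Carrying the baseline forward needs only a baseline value, and Table 1 schedules the baseline ODI at visit 1, where randomisation takes place. A randomised patient with no later ODI would enter with a change of zero. The planned rule therefore already allows all randomised patients with a baseline ODI to be analysed.

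**8. Economic set.** After baseline, the combination arm is first seen on Day 1-3 and the control arm on Day 7-8 (Table 1). A patient who leaves on Day 5 can qualify in the combination arm but not in the control arm.

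**The case against.** The strongest reply is the drop-out visit. Table 1 schedules endpoint evaluation and adverse reaction monitoring there, so a harmed patient who withdraws as planned has a post-baseline ODI and can enter both sets. A patient withdrawn for a serious reaction has also been judged unfit by someone, which implies contact. This stands, and it limits the point to treated patients who leave without any qualifying assessment. The telephone contact four weeks after drop-out does less: sections 2.2 and 2.8.3 describe it only for the exploratory evaluation of further NBT or surgery.

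It also stands that follow-up is undefined. The four-procedure count is conditional on one reading and does not demonstrate a gap in practice.

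A reader might infer three stronger things that the documents do not support:
- That every patient harmed early who leaves is missing from safety. The drop-out visit rules this out.
- That the planned 20% drop-out, 5 per arm, measures the loss. That figure covers attrition of all kinds over the whole trial, and most of those patients could remain in ITT.
- That entry to ITT is timed differently by arm. On the outcome-visit reading, the first visit is Day 12-14 in both arms. The Day 1-3 versus Day 7-8 difference bears on the economic rule, which is a separate set.

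Finally, the efficacy half is partly a matter of naming, since the set is openly defined. That is true, but the plan labels it ITT and makes it the main analysis.

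**Conclusion.** The point holds in a limited form. By stated rule, a treated patient without a qualifying follow-up is excluded from both efficacy and safety. The nesting follows from the wording alone. Its practical size is unknown and probably small: it depends on how follow-up and eligibility are read and on how many patients skip the drop-out visit, for which the documents give no figure. With 25 per arm, one such patient is 4 percentage points, enough to turn a single serious event into none. On the outcome-visit reading, the exposure that can go uncounted is larger in the combination arm (four procedures against one).

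The economic rule has its own, separate asymmetry by arm, arising from the visit calendar.

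None of this shows that the planned missing-data rule must be replaced. Widening ITT does not require that, and the merits of carrying the baseline forward are a different question.

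**What to change.** Change the definitions in section 2.9:
- **Safety set:** all randomised patients who received at least one trial procedure, analysed as treated, with no follow-up or efficacy condition.
- **ITT:** all randomised patients, analysed as allocated. The planned baseline-carried-forward rule can stay as it is.
- **Economic set:** all randomised patients, replacing the visit-2 condition. EQ-5D is collected at week 0, so the planned last-observation rule has a utility value to carry.
- **Present ITT definition, if kept:** rename it a modified full analysis set, define follow-up and eligibility for efficacy assessment, and use it only as a sensitivity analysis.

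The cost is wording in the protocol and analysis plan, with no extra patients, visits or data items. The change should be made before anyone sees who left and from which arm, because a set chosen after that is hard to defend.

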**Demographic information and pre-treatment characteristic analysis method**
Descriptive statistics will be conducted for demographic information and characteristics. Continuous data will be expressed using the number of observations, mean, standard deviation, median, 25% quantile, and 75% quantile. Categorical data will be expressed using frequency and percentage. For continuous data, independent *t*-test will be conducted to test the mean difference between groups if normality assumption is satisfied. If normality assumption is not satisfied, Wilcoxon's rank sum test will be conducted. Chi-Squared test will be conducted to test the mean difference between groups. If more than 25% cells have an expected frequency of less than 5, Fisher's exact test will be conducted.
2.

**Efficacy evaluation**
In the efficacy evaluation, ITT will be treated as the main analysis group, and PP sets will be treated as the secondary analysis group. All statistical analysis will be conducted as two-sided tests with a significance level of 5%. Two-sided 95% confidence interval will be presented. Descriptive statistics will be presented for each treatment group and visit. Descriptive statistics and 95% confidence intervals will be presented for differences between the baseline and each visit.

Among efficacy evaluation variables, missing values of continuous variables will be analyzed using baseline observation carried forward correction.

A. Analysis of primary endpoints

For symptoms of lumbosacral radiculopathy at each measurement time point, descriptive statistics (number of patients, mean, and standard deviation) of the ODI score and changes in ODI at the end of treatment (4 weeks) and follow-up (8 weeks) compared with the baseline will be presented.

Paired *t*-test or Wilcoxon's signed ranked test will be conducted for intra-group changes in ODI at the end of treatment (week 4) compared with the baseline (0) depending on the satisfaction of normality. An analysis of variance model that includes changes in ODI at the end of treatment compared with the baseline as effects and baseline ODI as covariates will be used to evaluate the effects in the treatment group compared with the control group. Differences in least-square mean between treatment and control groups will be calculated, and two-sided 95% confidence interval and *P* value for the differences will be presented.

B. Analysis of secondary endpoint

Changes in ODI at follow-up (8 weeks) compared with baselineAssessment of subjective pain intensity in patients with lumbosacral radiculopathy-Lumbosacral radiculopathy pain will be divided into lower back and lower extremity pain using NRS, MPQ, and K-RMDQAssessment of quality of life related to lumbosacral radiculopathy-Evaluation of overall quality of life using EQ-5D. The same analysis methods for primary endpoints will be used to analyze secondary endpoints

C. Exploratory efficacy evaluation

Evaluation related to additional NBT or surgery after completion of the study

The rate of additional treatment will be evaluated by assessing additional NBT or surgery performed for pain control within 4 weeks after the end of treatment. Chi-Squared test or Fisher's exact test will be performed to compare the rate of additional treatment and surgery between the groups.

**Rate of additional procedures = (patients who underwent additional procedures or surgeries/patients who completed the entire study)∗100**

Assessment of treatment early termination rate

Treatment early termination rate will be calculated for each group for patients who satisfied the criteria for early termination of treatment. Chi-Squared test or Fisher exact test will be performed to compare the rate of early termination of treatment between the groups.

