#### Exploratory effectiveness evaluation

2.8.3

1.Additional NBT or surgery for lumbosacral radiculopathy: All patients will be assessed if they underwent any additional NBT or surgical treatment related to lumbosacral radiculopathy on the last day of visit and at 4 weeks after the end of treatment. This assessment will be not conducted on those whose symptoms have improved and ended the study earlier. For patients who dropped out in the middle of the study, the assessment will be performed at 4 weeks after dropout. However, exploratory effectiveness evaluation for dropout participants can be conducted through telephone counseling instead of in-person visits.2.Early termination of treatment: Patients whose symptoms have improved during the study, who request to terminate treatment early, and who no longer require treatment at the discretion of the investigators will be separately evaluated for each group.3.Rescue medication usage: The number of uses, dosage, type, and administration point of rescue medications used between the clinical trial period and final evaluation period will be compared between the 2 groups.

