##### Dropout criteria

2.8.7.1

1.If the patient is under prescription of the following medications that are expected to affect the safety and effectiveness of NBT and acupotomy, the medications cannot be taken from the time of screening until the completion of the study.① Concurrent use of medications that are prohibited for use with medications used for NBT.Medications that are likely to cause serious side effects in drug interaction studies.Medications whose mutual use is restricted with disodium dexamethasone injection: asunaprevir, daclatasvir, dronedarone hydrochloride, eliglustat, grazoprevir, ibrutinib, nilotinib hydrochloride monohydrate, olaparib, osimertinib, palbociclib, rilpivirine, rivaroxaban, ticagrelor, ceritinib, ribociclib, venetoclax, elbasvir, BCG strain, cobimetinib, cicletanine, etc. (Other medications used for NBT do not cause side effects of serious grade in drug interaction studies)② Strong opioid, local anesthetic administered by another physician than the one for this clinical studyHowever, anti-inflammatory analgesics and muscle relaxants prescribed for necessary causes at the discretion of the clinician can be administered^[13]^ (See rescue medications).③ Medications that may pose a risk to the patient or cause bias in the results as judged by the clinical investigator2.The patient requests to discontinue interventions or withdraws consent for participation3.The patient is judged to be unfit to continue in the study due to serious adverse reactions/medication reactions4.Serious protocol violations such as inclusion/exclusion criteria are newly discovered during the study5.Patients in the NBT and acupotomy combination treatment group who do not meet the criteria for early termination but have not conducted 6 or more of the 8 planned acupotomy treatments6.Patients who do not meet the criteria for early termination but fail to conduct even one of the planned NBT7.Patients who are judged to be unfit to continue in the study for other reasons at the discretion of the clinical investigator

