**Rate of early termination = (patients who completed the study early/patients who completed the entire study)∗100**

Analysis of rescue medication use

Independent t-test or Wilcoxon's signed rank test will be conducted to compare the number and dose of use according to different types of rescue medication between the groups.

D. Classification and post hoc analysis of responders and nonresponders

Definition of responders

(1)Those with a minimal CID decrease of NRS 2.5 from the baseline to the date of evaluation. Therefore, responders will be defined as follows. For example, pain reduction of greater than NRS 2.5 will be defined as CID, and CID will be used to divide patients into responders and nonresponders.(2)Using the previously described criteria, patients who had improved symptoms and completed the study early will be considered as responders.

Post hoc analysis

Adequate post-hoc analysis will be conducted by a statistician for differences in treatment results for each treatment group using the responder and non-responder criteria.

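### The additional-procedure and early-termination rates are divided by study completers, although re-treatment is also collected from dropouts and ITT is the main efficacy set

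*Protocol article*

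**What the plan says.** Section 2.9, part C (exploratory efficacy evaluation), fixes two formulas, each multiplied by 100 and each compared between arms by a chi-squared or Fisher exact test:

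- Additional procedures: "patients who underwent additional procedures or surgeries/patients who completed the entire study".
- Early termination: "patients who completed the study early/patients who completed the entire study".

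Four other places bear on who belongs in these rates.

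- **Dropouts are assessed for re-treatment.** Section 2.8.3: "For patients who dropped out in the middle of the study, the assessment will be performed at 4 weeks after dropout". The Table 1 footnote agrees: "For patients who dropped out of the study, exploratory evaluation is conducted after 4 weeks from dropping out". Both allow a telephone contact. Both leave patients who improved and stopped early out of this assessment.
- **Analysis set.** Section 2.9: "In the efficacy evaluation, ITT will be treated as the main analysis group". The set is defined as follows: "The ITT group will include all patients who have been randomly assigned, undergo at least one follow-up", with eligibility for efficacy assessment added. Completion is not required.
- **Dropout criteria.** Section 2.8.7.1, item 5, removes combination-arm patients who "have not conducted 6 or more of the 8 planned acupotomy treatments". Item 6 removes a patient in either arm who misses a planned nerve block.
- **Early terminators.** Section 2.8.7.2 does not class them as withdrawn and treats them as compliant.

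**The concern.** The population from which re-treatment is collected and the population used as denominator do not match. An analyst who follows the formula has two choices for a dropout who had another block or surgery, and neither is sound.

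1. Count the event. The numerator then holds patients who are not in the denominator, and the no-event cell of the contingency table, obtained by subtraction, is too small.
2. Leave the event out. Data that the protocol requires are then unused, and the arms are compared among completers. Completion is decided after randomisation, and one dropout trigger (missed acupotomy sessions) exists in the combination arm only. This also departs from the plan's own choice of ITT for efficacy.

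The early-termination rate uses the same denominator, so it leaves out dropouts. It is also unclear whether someone who finished early has finished the entire study. If not, numerator and denominator are disjoint groups.

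At stake are two exploratory between-arm comparisons. One of them is the only listed outcome that counts surgery.

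**Working it through.** **Inputs from the documents.** Section 2.3 plans 20 patients per group and 20% dropout. This reproduces: 20/(1 − 0.20) = 25 per arm, 50 in total, so 5 dropouts per arm are expected. No re-treatment or early-termination frequency is given anywhere, so every event count below is an assumption. All 25 per arm are taken to be in the ITT set, and the re-treatment examples have no early terminators.

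**Re-treatment formulas.** Let D be dropouts, r re-treated dropouts, and R all re-treated patients in an arm of 25.

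- ITT rate: R/25
- All events over completers: R/(25 − D)
- Completers' events only: (R − r)/(25 − D)

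| Case | Arm | D | r | R | R/25 | R/(25 − D) | (R − r)/(25 − D) |
|---|---|---|---|---|---|---|---|
| a | Combination | 4 | 4 | 5 | 20.0% | 5/21 = 23.8% | 1/21 = 4.8% |
| a | NBT | 1 | 1 | 5 | 20.0% | 5/24 = 20.8% | 4/24 = 16.7% |
| b | Combination | 5 | 3 | 5 | 20.0% | 5/20 = 25.0% | 2/20 = 10.0% |
| b | NBT | 2 | 0 | 4 | 16.0% | 4/23 = 17.4% | 4/23 = 17.4% |
| c | Each arm | 5 | 2 | 5 | 20.0% | 5/20 = 25.0% | 3/20 = 15.0% |

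- Case a: equal true rates become unequal on either reading.
- Case b: the order of the arms depends on which reading the analyst takes.
- Case c: with the same dropout pattern in both arms the level is wrong, but there is no false difference.

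**The table error.** In case a, 5/21 implies 21 − 5 = 16 combination patients without re-treatment. In fact 25 − 5 = 20 had none.

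**Inflation at the planned dropout.** When dropouts' events are counted, the rate is multiplied by 25/20 = 1.25.

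**Early termination.** Assume E = 5 early terminators and D = 5 dropouts of 25.

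- Early terminators outside the denominator: 5/(25 − 5 − 5) = 5/15 = 33.3%
- Early terminators inside the denominator: 5/(25 − 5) = 5/20 = 25.0%
- All randomised: 5/25 = 20.0%

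On the first reading the result is not bounded by 100%: with E = 12 and D = 5 it is 12/8 = 150%, which no contingency table can hold.

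**Effect on the tests.** Two-sided Fisher p-values are:

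- Case a: 1.00 (5/21 v 5/24) and 0.35 (1/21 v 4/24). With 5/25 v 5/25, 1.00.
- Case b: 0.71 (5/20 v 4/23) and 0.67 (2/20 v 4/23). With 5/25 v 4/25, 1.00.

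The estimates move, but no test conclusion changes at the 5% level.

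**The case against.** The strongest defence is that a completer denominator has some logic. The rate is meant to count procedures within 4 weeks after the end of treatment. Patients who finish the schedule share that window, whereas a dropout's 4 weeks start at dropout. This stands as a reason to show dropouts' events separately. It does not explain why their data are collected for a rate that has no place for them, and it does not reconcile the formula with ITT.

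Second, the practical effect is small: these are exploratory outcomes in a 50-patient preliminary study, and none of the illustrations changes a test result. That stands and limits the severity.

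Third, the arm differences come from chosen splits. Case a has every dropout re-treated, and case b needs 3 of 5 against 0 of 2. That also stands. A reader might infer that the formula will favour a particular arm. The documents do not support this: item 5 adds a trigger in the combination arm, but item 6 applies to both arms, and nothing indicates how far dropout or re-treatment among dropouts will differ.

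Fourth, a reader might conclude that the early-termination formula is simply not a proportion. That holds only if early terminators are outside the denominator. Section 2.8.7.2 treats them as compliant, which supports the other reading, under which it is an ordinary proportion. Even then dropouts are left out.

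Finally, the Discussion mentions fewer operations as a hoped-for benefit. That is a closing remark, not a stated trial objective, and it does not raise the standing of this endpoint.

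**Conclusion.** The point holds as an error in two stated formulas for exploratory endpoints. For additional procedures, the mismatch between data collection and denominator is plain in the text, and neither way of handling dropouts' events gives a valid ITT comparison. For early termination, the denominator wrongly leaves out dropouts, and the term for completing the entire study is undefined, so the same data can give 33.3% or 25.0% against 20.0% of those randomised.

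At the planned dropout, a rate that counts dropouts' events is inflated by a factor of 1.25. Any arm difference, and its direction, depends on event counts that the documents do not give; with equal patterns there is none. The primary week-4 ODI analysis and the sample size are unaffected. The change is worth making because it is cheap, not because a main conclusion depends on it.

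**What to change.** In section 2.9 C:

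1. Use the ITT set per arm as the denominator of both rates, and use the same counts in the chi-squared or Fisher tables. Numerators count ITT patients only.
2. For additional procedures, include dropouts' events in the numerator and also show them separately, because their 4-week window starts at dropout.
3. Early terminators are not assessed for re-treatment. Count them as not re-treated, show their number per arm, and repeat the rate among assessed patients only as a sensitivity analysis.

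The cost is the wording of two formulas and one rule. No new data are needed, since re-treatment in dropouts is already to be collected.

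Two downsides remain. The dropouts' window differs from the completers' window. The early-terminator rule is an assumption: with 5 re-treated patients and 5 unassessed early terminators of 25, the main rate is 5/25 = 20.0% and the sensitivity rate is 5/20 = 25.0%. The sensitivity rate itself conditions on a post-randomisation event, so it should not replace the main one.
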